### Qualitative data analysis

Transcripts of interview data will be analysed via Thematic Analysis using the framework approach [49]. Framework analysis was developed to meet information needs and to provide practical outcomes and recommendations [50]. It offers a highly visible and systematic approach to data analysis, showing very clearly how findings are derived. Analysis will follow the five stages of framework analysis; familiarisation with the data; identifying a thematic framework; indexing the data; charting the data; and mapping and interpretation [51]. To monitor and limit the possible bias of a single-analyst perspective, additional members of the research team with experience in qualitative methods will examine a sample of transcripts to compare their perceptions of the interview data and analysis with the main analyst’s interpretation. Themes will be discussed and refined further in multidisciplinary research team meetings.

NPT [31] provides a framework for understanding the barriers and facilitating processes that underlie the implementation and integration of complex interventions into healthcare systems. This will help make sense of the qualitative data and draw conclusions relating to how readily COPESS might be implemented and embedded into health care systems [31, 51]. The theory identifies four key processes that underlie the adoption of new interventions; coherence of intervention; cognitive participation; collective action; and reflexive monitoring. Previous research has shown that NPT can be applied effectively to qualitative data in healthcare contexts to aid interpretation [52]. NPT will be used to map the links between qualitative themes and the core processes outlined in NPT. This process will be aided through use of the NPT toolkit (normalizationprocess.org) and application of the NPT statements generated by May and colleagues [51]. To further promote integrity and rigor during the data analysis process, field notes will be written immediately after interviews and a reflective diary maintained. Thus, aiming to reduce the potential for the researcher’s values, beliefs and preconceptions to influence subsequent findings [31, 52].

### Data handling

All confidential data will be stored securely on the University research centre site with strictly limited access. Participants will be allocated an ID code which will be used on documents such as questionnaires to maintain confidentiality and minimise the use of personal data. The feasibility trial Sponsor is Liverpool John Moores University who takes primary responsibility for ensuring that the design of the study meets appropriate standards in accordance with Good Clinical Practice (GCP) guidelines. All data will be handled according to the General Data Protection Regulation (GDPR) 2018. It was agreed by the Project Steering Group that a Data Monitoring Committee was not required due to the research being a feasibility trial.

### Safety monitoring

Adverse events and risk standardised operating procedures will be developed and will be followed by all researchers and therapists working on the feasibility trial. Adverse events are defined as significant negative episodes, or significant deterioration in condition, which happen to participants during their time in the feasibility trial. These will be reported by research assistants and trial therapists to senior trial staff, who will ascertain whether these are thought to be linked to participation in the feasibility trial, and keep records of each event on an adverse events database. The Adverse Experiences in Psychotherapy (AEP) self-report measure [53] will identify adverse experiences liable to occur within psychological therapy. All serious adverse events (SAE) of an unexpected and unrelated nature will be reported to the main Research Ethics Committee, the study Sponsor and Trial Steering Committee (TSC). Suicide risk will be closely monitored. If the individual is considered to be high risk, the participant’s GP will be contacted and information passed to them within two working days. The participant will also be given advice about local crisis teams, and other relevant support services. In cases where SAE are potentially linked to the feasibility trial, withdrawal of participants, halting or terminating the feasibility trial will be considered as required.

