## Aims

The aim of this study is to examine the feasibility and acceptability of delivering the COPESS intervention in a community setting, as well as to assess the feasibility and acceptability of the trial procedures themselves, with a view to future implementation in a full-scale efficacy trial. The key outcomes concern methodological, procedural and clinical uncertainties [32–34] such as estimates of recruitment and retention rates; feasibility and acceptability of data collection instruments and data collection procedures; feasibility, acceptability and safety of the intervention.

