### Design

The study is a single-blind, randomised controlled feasibility trial with an embedded qualitative process evaluation. Participants will be randomised 1:1 to receive COPESS plus treatment-as-usual (TAU) or TAU alone.

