### Interventions

#### COPESS plus TAU

COPESS consists of four 50-min weekly sessions of face to face or remote psychological therapy. A further follow-up session is offered 4 weeks after the end of therapy. Therapy is usually completed within 8 weeks, but variations from the expected schedule, associated reasons and drop-out rates will be monitored. Mersey Care NHS Foundation Trust will train five of their current therapists (Mental Health Nurses and Assistant Psychologists) in the COPESS therapy. The therapy involves working collaboratively with a patient to identify patterns or conflicts in emotional experiences and interpersonal relationships, linked to depressed mood and acts of self-harm. The therapist works with the patient to build a shared understanding of these experiences. The first session will focus on the participant’s most recent episode of self-harm and the interpersonal events that precipitated the episode, and the participant’s associated low mood. Risk assessment and safety planning will also be incorporated into the initial session. The three remaining sessions will focus upon the links between mood, relationship difficulties and self-harm. PIT techniques include picking up cues, staying with and exploring feelings about relationships and interpersonal problem-solving in the here and now. CAT techniques will be used to help the participant to map out and understand the reciprocal nature of relationships.

Due to the on-going impact of COVID-19 participants in the intervention arm will have the option of remote (via an online method such as Zoom or Skype or the telephone) or face-to-face therapy sessions in the participant’s home or in a community setting, once pandemic-related restrictions allow this option. There may be a difference in effectiveness of the intervention depending on whether COPESS is delivered remotely or face to face, and this will be assessed via comparison of quantitative data outcomes and through qualitative interviews**.** This choice will be solely participant preference and will not be part of the randomisation process. Safety for the therapist/researcher and/or mobility for the patient will be reviewed throughout the recruitment period.

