### Treatment-as-usual (TAU)

There will be no restrictions on care provided as TAU. Participants randomised to TAU will be provided with information about how to refer to local statutory or non-statutory services and GPs will be encouraged to follow the NICE guidance on care for people who self-harm.^4^

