### Secondary outcomes measures

Participants will complete a batch of standardised questionnaires at follow-up assessments (see below) to be conducted at 4, 8 and 12 weeks post-randomisation (Table 1 shows the full assessment schedule). Participants will be invited to follow-up assessments unless they have completely withdrawn from the feasibility trial. Questionnaires used for the secondary outcome measures will help to:
Assess the feasibility of delivering these measures within an RCT context;Assess rates of missing data as this will inform the use of these outcomes in a full trial;Estimate variance in these outcomes as this will guide the power calculations for the full trial.

**Table 1 Tab1:** Timing of outcome measurement

***List of questionnaire***	***Baseline***	***Follow-up 1***	***Follow-up 2***	***Follow-up 3***
*Demographic information*	*X*			
*ABUSI*	*X*	*X*	*X*	*X*
*AEP Form (A/B)*		*X*		*X*
*Beck Depression Inventory*	*X*	*X*	*X*	*X*
*CORE-10*	*X*	*X*	*X*	*X*
*ERQ*	*X*	*X*	*X*	*X*
*EQ-5D*	*X*			*X*
*HAq-II*	*X*	*X*	*X*	*X*
*SITBI 2.1*	*X*	*X*	*X*	*X*
*CSRI*				*X*

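### Adverse event database counts are not comparable between arms, because trial therapists report events only for COPESS participants (up to 8 scheduled reporting contacts against 3 in TAU)

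*Protocol article*

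**What the plan says.** All references are to the protocol article.

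- **Safety monitoring** gives a broad definition that rests on judgement: "Adverse events are defined as significant negative episodes, or significant deterioration in condition, which happen to participants during their time in the feasibility trial". On the route it says: "These will be reported by research assistants and trial therapists to senior trial staff". Senior staff judge whether each event is linked to trial participation and keep the records in one adverse events database.
- **COPESS plus TAU** sets the therapist contacts: "COPESS consists of four 50-min weekly sessions of face to face or remote psychological therapy", and then "A further follow-up session is offered 4 weeks after the end of therapy".
- **Secondary outcomes measures** sets the research contacts, the same in both arms: "to be conducted at 4, 8 and 12 weeks post-randomisation".
- **Treatment-as-usual** provides no trial therapist: "There will be no restrictions on care provided as TAU". TAU participants may see other clinicians, but Safety monitoring does not name those clinicians as reporters.
- **Aims** lists among the key outcomes "feasibility, acceptability and safety of the intervention".
- **Design** gives the allocation: "Participants will be randomised 1:1 to receive COPESS plus treatment-as-usual (TAU) or TAU alone".

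The article does not say that reports are recorded by source or limited to occasions shared by the two arms.

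**The concern.** One of the two named reporting routes exists in one arm only. The therapy is also likely to bring events to light. Its first session centres on the latest self-harm episode and includes risk assessment and safety planning, and the later sessions link mood, relationships and self-harm. Under a broad definition, such conversations can surface episodes that a TAU participant has no matching occasion to mention.

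A further asymmetry follows withdrawal. The section on withdrawal lets COPESS therapy continue after a participant leaves the research, so that participant may still have a trial reporter when a TAU participant who leaves has none. The article does not say whether such reports would be entered.

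At stake is how the database is read when a full trial is planned. An excess under COPESS could be taken for harm when it is only better capture, or a real excess could be put down to reporting. If the source is not recorded at the time, it cannot be recovered reliably later.

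**Working it through.** The article states no count of reporting contacts, so there is no figure of its own to reproduce on this point.

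**Step 1. Scheduled contacts.**
- Therapist (COPESS plus TAU section): 4 weekly + 1 follow-up = 5, COPESS only.
- Research (Secondary outcomes measures): 3, both arms.
- COPESS maximum 5 + 3 = 8; TAU 3; ratio 8/3 = 2.67.

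Eight is a ceiling. With s sessions attended the contact ratio is (s + 3)/3, which gives 1.00, 1.33, 1.67, 2.00, 2.33 and 2.67 for s = 0 to 5. The acceptability criterion in Primary outcome asks only that more than 40% attend all sessions.

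**Step 2. Upper bound on the recorded ratio.** Assume equal true risk, and that each contact independently picks up a given event with probability q. The article gives no q. Then P(recorded) = 1 − (1 − q)^k, with k = 8 or 3.

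| q | COPESS | TAU | Ratio |
|---|---|---|---|
| 0.2 | 0.832 | 0.488 | 1.71 |
| 0.3 | 0.942 | 0.657 | 1.43 |
| 0.5 | 0.996 | 0.875 | 1.14 |
| 0.8 | 1.000 | 0.992 | 1.01 |

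This overstates the effect at low and moderate q, because it lets a session detect an event that has not yet happened.

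**Step 3. Allow for timing.** Assume sessions at weeks 1, 2, 3, 4 and 8, assessments at weeks 4, 8 and 12, full attendance, and events uniform over 12 weeks. Contacts remaining after an event:

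| Event in week interval | Width (weeks) | COPESS | TAU |
|---|---|---|---|
| 0–1 | 1 | 8 | 3 |
| 1–2 | 1 | 7 | 3 |
| 2–3 | 1 | 6 | 3 |
| 3–4 | 1 | 5 | 3 |
| 4–8 | 4 | 3 | 2 |
| 8–12 | 4 | 1 | 1 |

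Mean contacts after an event: COPESS (8 + 7 + 6 + 5 + 4×3 + 4×1)/12 = 42/12 = 3.5; TAU (4×3 + 4×2 + 4×1)/12 = 24/12 = 2.0.

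Averaging 1 − (1 − q)^k over the intervals, for example at q = 0.2:
- COPESS: (0.832 + 0.790 + 0.738 + 0.672 + 4×0.488 + 4×0.200)/12 = 0.482
- TAU: (4×0.488 + 4×0.360 + 4×0.200)/12 = 0.349
- Ratio: 0.482/0.349 = 1.38

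| q | COPESS | TAU | Ratio |
|---|---|---|---|
| 0.2 | 0.482 | 0.349 | 1.38 |
| 0.3 | 0.617 | 0.489 | 1.26 |
| 0.5 | 0.787 | 0.708 | 1.11 |
| 0.8 | 0.931 | 0.917 | 1.01 |

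**Step 4. Partial attendance.** If only the sessions at weeks 1 and 2 are attended, COPESS has 5, 4, 3, 3, 2 and 1 contacts in the six intervals. At q = 0.2 its average is (0.672 + 0.590 + 2×0.488 + 4×0.360 + 4×0.200)/12 = 0.373, and the ratio is 0.373/0.349 = 1.07.

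**Step 5. In events.** With about 30 per arm (60 at 1:1) and an assumed true risk of 30%, each arm has 30 × 0.30 = 9 true events. At q = 0.2 and full attendance, expected recorded events are 9 × 0.482 = 4.3 against 9 × 0.349 = 3.1.

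**Step 6. Common source only.** Counting reports from the three shared assessments gives 3 contacts against 3, and the ratio is 1.0 by construction.

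**The case against.** The case on the other side is substantial.

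- **No between-arm comparison of adverse events is stated.** Statistical analysis plans no test of effectiveness, and the by-group summaries it names are repetition of self-harm, depressive symptoms and urges. The criteria in Primary outcome include none on safety. Events are judged one by one for a link to the trial. This stands. A reader might infer that safety can be judged only against TAU, but the article does not say so.
- **Safety-relevant data already exist on a common schedule.** Table 1 lists SITBI, BDI, ABUSI and CORE-10 at all three follow-ups and AEP at the first and third, with no arm restriction shown. This also stands. A reader might infer that any statement on the safety of COPESS is biased, and that is not supported. SITBI summaries are not affected in this way, and a description of events within COPESS gains from the extra reports. These measures still do not make the database counts comparable.
- **GPs are another route.** For self-referred participants in either arm, GP contact is meant to help capture events. That does not remove the therapist-only stream.
- **Operating procedures are still to be developed and may settle the details.** They may, and the lack of a source field in an article is not itself an error. The point rests on what the article does state: two reporting routes, one of them confined to one arm, feeding one database.
- **The numbers are assumed.** They are, and Steps 3 and 4 show how far timing and attendance shrink them.
- **Limiting by-arm tables to attended assessments could hide serious events** in people who die, are in hospital or drop out. This is right, and the fix allows for it.

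**Conclusion.** The point holds as a limit on what the database counts can support. As written, ascertainment is unequal between arms, nothing shown equalises it, and safety of the intervention is a key outcome. With equal true risk, raw counts would tend to run higher under COPESS.

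The size is not known. At full attendance and with event timing allowed for, the recorded ratio is about 1.4, 1.3 and 1.1 at q = 0.2, 0.3 and 0.5. It is near 1 if the assessments already capture most events, and smaller with partial attendance. These figures rest on an assumed q, independent contacts, assumed session weeks and uniform event times. In a trial of this size the gap is likely to be a few events at most. No planned analysis is shown to be wrong; this is a cheap improvement that has to be made before data are collected.

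**What to change.** 1. Add a field to the adverse events database for the source of each report (research assessment, therapist, GP or other).
2. Ask the same adverse-event question in both arms at the 4-, 8- and 12-week assessments.
3. State that any between-arm summary of non-serious adverse events uses that common source, and that therapist-only reports are listed separately as COPESS-only information.
4. Keep all serious adverse events, from every source, in the by-arm table, with the source shown.

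Reporting and follow-up of individual events are unchanged. The cost is one database field, one added question per assessment and a sentence or two in the analysis section, with no extra visits. The small downside is that non-serious events known only to therapists sit outside the comparative table, though they are still listed.

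### The only stated route for serious adverse events to the ethics committee, sponsor and steering committee covers unrelated events, while possible halting of the trial is tied to linked ones

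*Protocol article*

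**What the plan says.** The relevant text is almost all in the Safety monitoring section of the protocol article.

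- **Internal route.** Of adverse events in general the section says: "These will be reported by research assistants and trial therapists to senior trial staff, who will ascertain whether these are thought to be linked" to taking part. The same staff are to "keep records of each event on an adverse events database".
- **External route.** For SAEs it says: "All serious adverse events (SAE) of an unexpected and unrelated nature will be reported to the main Research Ethics Committee". The sentence goes on to name the sponsor and the TSC as further recipients.
- **Consequence for the trial.** The section ends: "In cases where SAE are potentially linked to the feasibility trial, withdrawal of participants, halting or terminating the feasibility trial will be considered as required".

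Two other sections give context. Data handling records the decision that "a Data Monitoring Committee was not required", because this is a feasibility trial. Aims lists "feasibility, acceptability and safety of the intervention" among the key outcomes.

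**The concern.** The section has senior trial staff judge whether each event is linked to the trial. Such a judgement would be expected to pick out linked events for closer scrutiny. The external reporting sentence uses it the other way round: the SAEs it sends on are those judged not to be linked. The closing sentence then treats linked SAEs as the ones that could lead to the trial being halted or ended. The two sentences therefore point at opposite sets of events.

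The stakes are participant safety and oversight. Everyone enrolled has self-harmed within the last 6 months and scores 14 or more on the BDI-II (Inclusion criteria), and the Abstract describes people who self-harm as being at high risk of later suicide. With no Data Monitoring Committee, the ethics committee, sponsor and TSC are the only oversight of SAEs that the article describes outside the trial team. Anyone working from this text alone would find no instruction to tell those bodies about an SAE thought to be caused by the therapy or by the recruitment procedures.

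**Working it through.** No arithmetic applies. The check sets every statement on the handling of adverse events side by side and sorts SAEs by the rule as written.

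**Step 1: find every reporting statement.**

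- *Safety monitoring*: one internal route (senior trial staff and the database), one external route (ethics committee, sponsor, TSC), and one sentence on the consequences of linked SAEs.
- *Recruitment of participants*: adverse events, including reactions linked to recruitment, will be monitored throughout, and the GP of a self-referred participant is contacted partly so that adverse events can be captured. No oversight body is named as a recipient.
- *Safety monitoring* and Table 1: the AEP self-report measure collects adverse experiences of therapy. It is a data source and not a reporting route.
- *Data handling*: no Data Monitoring Committee.

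There is therefore one external reporting sentence for SAEs in the whole document.

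**Step 2: sort SAEs by that sentence.** It sets two conditions, unexpected and unrelated, and both must hold.

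| SAE class | Senior trial staff and database | Stated route to ethics committee, sponsor and TSC | Covered by the closing sentence on halting |
|---|---|---|---|
| Unexpected, unrelated | Yes | Yes | No |
| Unexpected, related | Yes | None stated | Yes |
| Expected, related | Yes | None stated | Yes |
| Expected, unrelated | Yes | None stated | No |

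**Step 3: compare the last two columns.** They share no row. The one class with a stated external route is not covered by the sentence on halting. The two classes that sentence does cover have no stated external route.

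**Step 4: look for a reconciling statement.** Between the external reporting sentence and the closing sentence stand three sentences, on suicide risk monitoring, contact with the GP and advice on crisis support. None extends the route to related SAEs, and no other section does so. The closing sentence itself, "In cases where SAE are potentially linked to the feasibility trial" and what follows, does not say who considers halting or who is told.

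**The case against.** The strongest reply is that this is a slip of the pen and not a policy. A team that wished to keep related SAEs from its oversight bodies would hardly have staff judge relatedness and then close by contemplating termination for linked SAEs. That is probably right, and it means the point should be classed as an internal contradiction and not as a deliberate design choice. It does not remove the point: the slip reverses the meaning of an operative rule.

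A second reply is that the working rule lies elsewhere. The article says that operating procedures for adverse events and risk will be developed, mentions a safety protocol in the Qualitative study section, and reports ethics review of the procedures for managing risk and distress. None of these is shown. They may well be correct, so any practical harm depends on staff following this sentence and not a better one. But the point concerns what the article states and contradicts, not a detail it leaves out. Procedures still to be written could also carry the error forward.

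A third reply is that the text never says *only*. That is true. The restriction follows because this is the sole external reporting sentence and it defines its own class of events.

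Some stronger readings are tempting, and the document does not support them:

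- *Related SAEs go unreported, so the halting decision has no trigger.* They still reach senior trial staff and the database, and the closing sentence lets staff act on them. What is missing is a stated route to the oversight bodies.
- *The ethics committee, sponsor and TSC are the only independent look at harm.* The article does not describe the independence of the sponsor or the TSC. It supports only the statement that they are the sole oversight of SAEs described outside the trial team.
- *Unrelated SAEs cannot inform a decision to halt.* An imbalance between arms in events judged unrelated could be informative.
- *The TSC should receive all SAEs by arm.* That is a preference, and its absence is not an error in this document.

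**Conclusion.** The point holds as an internal contradiction in an operative safety rule and should be corrected. As written, one of the four SAE classes has a stated route to the ethics committee, sponsor and TSC. It is an unrelated class, and neither related class has such a route. The events for which halting or termination would be considered are therefore outside the stated reporting route.

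The size is qualitative. No estimate, progression criterion or sample size figure depends on the sentence. The weight comes from the high-risk population, the absence of a Data Monitoring Committee, and the place of intervention safety among the key outcomes.

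The conclusion rests on two readings: that the single external reporting sentence is meant to define what is reported, and that *potentially linked* in the closing sentence and *related* in the reporting sentence refer to the same judgement. Both are the natural readings. Whether the unseen operating procedures already state a different rule cannot be determined from the article, and a correct procedure would still leave the article's own rule in need of correction.

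**What to change.** Reconcile the external reporting sentence with the closing sentence of Safety monitoring, so that SAEs judged related or potentially linked to the trial fall within the stated reporting route to the ethics committee, sponsor and TSC. If *unrelated* was a slip for *related*, say so and correct it. Because the present sentence also requires the event to be unexpected, the revised wording should make clear whether expected SAEs that are linked to the trial are included; changing the one word alone would leave them without a stated route.

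Then check the safety operating procedure against the corrected sentence so that both describe the same events. The cost is a one-sentence amendment and a check of the procedure, with negligible added workload and no effect on design, sample size or analysis. No change to the provision on withdrawal, halting or termination is proposed here.
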